#### Analysis

Consent rates, recruitment rates, attrition, missing data rates and intervention fidelity will be reported as proportions with 95% CIs. The analysis of clinical outcome measures will be descriptive, reported as means and SD or medians and IQRs if not normally distributed for continuous outcomes and numbers and percentages for binary and categorical variables. Between-group mean differences will be reported together with 95% CIs. No formal statistical testing will be undertaken.

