### Randomisation, blinding and allocation concealment

Randomisation will take place once patient and caregiver participant consent forms and baseline questionnaire packs have been completed, received and checked by a member of the central trial team at Norwich Clinical Trials Unit (NCTU). The randomisation scheme will be generated by the NCTU Trial Manager and the allocated group will be notified by email to the site trial team. Randomisation will be stratified at the individual-dyad level (approximately 2:1) by:

SiteAge of patient (< or > and equal to 65 years).

The allocation is computer generated so will not be known prior to randomisation. Allocation is concealed prior to randomisation to prevent selection (or treatment allocation) bias.

Due to the participatory nature of rehabilitation, it will not be possible to blind patients, caregivers or treating healthcare professionals to group allocation after randomisation. The trial PIS has presented intervention equipoise. Therefore, while not possible to blind, we have aimed to limit expectation bias through careful selection of PIS wording for participants.

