### Secondary outcomes

Outcome data completeness—by analysis and reporting on completion rates (baseline and 3 months post-randomisation) of: *Patient Participants*: Musculoskeletal-Health Questionnaire (MSK-HQ)^22^; numerical rating scale for pain and fatigue^23^; self-efficacy, assessed using the General Self-Efficacy Scale^24^; psychological distress (depression), assessed using the Centre for Epidemiologic Studies Depression Scale (CES-D)^25^; HRQoL assessed using the EQ-5D-5 level questionnaire (EQ-5D-5L)^26^; self-reported health resource use questionnaire; adverse events. *Caregiver Participants*: EQ-5D-5L^26^; CES-D^25^; the Zarit Burden Interview Scale—12-item version^27^; Leisure Time Satisfaction questionnaire^28^; self-reported health resource use questionnaire; adverse events.Signal of effectiveness—by calculating and reporting effect size measurement of the above outcome measures.

These measures were selected due to their robust psychometric properties and acceptable patient and caregiver burden as confirmed by our study patient representatives/clinician feedback. They reflect relevant core outcome sets including: lower limb osteoarthritis,^29^ low back pain^30^ and general musculoskeletal disease.^31^ Caregiver outcomes mirror the domains of importance reported through previous qualitative findings.^9^

Baseline assessment will be undertaken after patient and caregiver participants have signed the consent form, prior to randomisation. Patient and caregiver participants will be provided with a paper-based questionnaire to complete in their recruitment information pack. Baseline data collected will include: (for patient and caregiver): age, sex, ethnicity, occupational status (current or past if retired), medical comorbidities, presenting musculoskeletal pathology(ies); and for patient, duration of symptoms relationship of caregiver to patient; and for caregiver: duration of caregiving, whether caregiver for another person, whether lives with patient.

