### Data analysis

#### Sample size

In total, 80 participant dyads (80 patients/80 caregivers) will be recruited. This sample size will be sufficient to answer our feasibility objectives and assess the a priori progression criteria (table 2).^32^ This number will also allow each site to test the JOINT SUPPORT programme in at least two complete cycles. This sample size follows recommendations^33^ for designing feasibility trials that aim to detect a small–medium standardised effect size (where the definitive trial will be designed with 80% power and two-sided 5% significance).^32 34^

**Table 2 T2:** Feasibility study stop–go, traffic light, progression criteria

	Green (go)	Amber (amend)	Red (stop)
Recruitment	>30% of the patients screened across the sites in 12 months would be eligible	20%–30% would be eligible	<20% would be eligible
Intervention fidelity (healthcare professionals)	>70% of the participant-dyads compliant with their allocated intervention (five face-to-face sessions and booster phone call) as randomised	50%–70% received intervention as randomised	<50% received intervention as randomised
Intervention fidelity (caregivers)	>90% of the participants adopted elements of JOINT SUPPORT programme post-last session	60%–90% adopted JOINT SUPPORT post-last session	<60% adopted elements post-last session
Randomisation acceptability	>40% of the eligible participants consent to be randomised	20%–40% would be randomised	<20% would be randomised
Contamination	<5% of the participants in either group received majority of their allocated treatment cross-over	5%–10% of the participants cross-over	>10% of the participants cross-over
Data collection completion	<15% missing outcome questionnaires for whatever reason at 3-month data collection	15%–30% missing questionnaires	>30% missing questionnaires

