#### Eligibility

The embedded qualitative study is optional for participants. Patients and caregivers will be able to express an interest to be approached regarding the qualitative substudy on the main study consent form at the beginning of the study. The sample will consist of patient–caregiver dyads and physiotherapists and occupational therapists who have delivered the JOINT SUPPORT intervention.

Dyads who have agreed to be contacted for an interview will be purposively sampled to ensure a maximum variation in: age, gender, presenting musculoskeletal pathology, ethnicity, duration of disability, severity of disability (as measured by the baseline MSK-HQ),^22^ relationship of caregiver to patient and duration the caregiver has been caring for the patient. Our intention is for caregivers and patients to be interviewed separately to enable them to more freely express their views but we will interview as a dyad if this is expressly requested.

We anticipate around 24 interviews will be conducted, involving approximately 12 patients/12 caregivers from the JOINT SUPPORT programme and approximately 8 caregivers/8 patients from the TAU group across the sites. Based on our previous research,^9^ this sample size should ensure a range of different viewpoints to reach information power^36^ to answer our feasibility questions.

The healthcare professionals delivering the JOINT SUPPORT intervention will be invited to participate in the voluntary interviews within 3 months of completing one participant through the JOINT SUPPORT programme. A minimum target of one physiotherapist and one occupational therapist who delivered the intervention will be invited to be interviewed from each site (eight participants in total). This will provide a range of contexts from different professional backgrounds. The healthcare professionals will be sent a PIS outlining the objectives and processes involved with this optional substudy. They will be asked to contact the research team by email if they are interested in participating. Those who express an interest will be contacted to arrange a mutually convenient time to conduct the interview.

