The acceptability of the care (both groups)	Would you be happy to talk me through your treatment? As X’s carer, what was your impression of the care. For both of you, what was helpful and less helpful to your care?
Group-based JOINT SUPPORT programme and telephone booster calls (experimental group)	How far did you find the JOINT SUPPORT programme helpful—for both of you. Can you give specific examples? What didn’t work as well? Did you get the telephone calls from the trial team? Can you remember what you talked about? Can you give specific examples of what was helpful, and l helpful? Was there any advice that confused you or you weren't clear about?
What the strengths of the experimental intervention (perceived effectiveness)	What were the most helpful/good-bits of your JOINT SUPPORT intervention? What was good about it What didn’t you like about it?
What the weaknesses of the experimental intervention	What were the less helpful/worse bits of the JOINT SUPPORT intervention?
What modifications they may recommend to interventions received (standard care and experimental groups)	What could we improve? (prompt: What do you think is lacking?) How do you think we could better support you and your carer to support you with chronic pain?
The risk of intervention contamination between the groups	Did you talk to any other patients or caregivers while in hospital about the intervention? Was there any discussion between those who received it and did not receive it?
The ease and convenience of the data collection processes (baseline and 3 months) (all participants)	As you were part of a trial, we had to collect a lot of measurements. Can you talk me through what these were? How easy were they? How convenient were they? Overall, do you have any points to make about the testing?
Applicability of the methods and measures used	How did you manage with the questionnaires we gave you at the start of the study and at the end in the post? Were they easy to complete or do you remember them being a problem?

**Table 4 T4:** Interview topic guide for the healthcare professional interviews

The interview will be structured on the following areas of interest	Sample questions
Introduction (Perceived effectiveness)	Overall, could you share your experiences of being involved with our research?
The randomised to either group	How did you feel about 50% of the patients not receiving the JOINT SUPPORT intervention but getting normal care? Did this ‘sit easy’ with you?

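### The signal of effectiveness is described only as between-group mean differences, most naturally read as unadjusted, although baseline scores and stratification factors are available to sharpen it

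*Protocol article*

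**What the plan says.** All references are to the protocol article.

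- **Objective.** The signal of clinical effectiveness is a secondary objective. Under Secondary outcomes it is to be delivered as follows: "Signal of effectiveness—by calculating and reporting effect size measurement of the above outcome measures".
- **Contrast.** The Analysis section calls the clinical outcome analysis descriptive, adds "Between-group mean differences will be reported together with 95% CIs", and rules out formal testing. It names no model, baseline covariate or stratification factor. It does not use the word unadjusted either.
- **Summaries.** Continuous outcomes are to be "reported as means and SD or medians and IQRs if not normally distributed for continuous outcomes".
- **Data available.** The Secondary outcomes section lists the same instruments at baseline and at 3 months, and places the baseline assessment after consent and before randomisation.
- **Design.** "Randomisation will be stratified at the individual-dyad level (approximately 2:1) by" site and patient age, cut at 65 years.
- **Size.** "In total, 80 participant dyads (80 patients/80 caregivers) will be recruited".

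**The concern.** A paragraph that calls the analysis descriptive and then promises mean differences will usually be carried out as a simple comparison of 3-month means. That leaves out two things the trial already has: each participant's baseline score on the same scale, and the factors used to stratify the randomisation.

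In 80 dyads split about 2:1, a chance difference between the arms at baseline can be noticeable, and a raw 3-month difference carries it. Where baseline predicts outcome, the interval is also wider than the data require. The reported effect size, which readers will look at when a definitive trial is considered, is then blurrier than it need be.

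The summary rule adds a smaller reporting problem. It is an either/or rule, so a skewed scale would be reported without its SD. The SD is what a standardised effect needs, and what the sample size of the definitive trial will need.

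**Working it through.** **The plan's own figure.** The Sample size section rests 80 dyads on published recommendations for feasibility trials. It gives no numeric effect, SD or precision target, so there is no planned interval width to reproduce.

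**Inputs**

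- Total of 80 dyads, split 2:1 as about 53 and 27 (Sample size; Randomisation). The larger arm is not named, but the half-width does not depend on which it is.
- Missing questionnaires: 15%, the green limit in Table 2. 53 × 0.85 ≈ 45 and 27 × 0.85 ≈ 23, so N = 68.
- Four sites, inferred. One physiotherapist and one occupational therapist "will be invited to be interviewed from each site (eight participants in total"), and 8 / 2 = 4.
- Covariates: baseline score (1), site (3 terms), age group (1), so q = 5.
- Baseline-outcome correlation r: **assumed**, 0 to 0.7. Site and age group are assumed to explain nothing beyond baseline.

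**Formulas, in outcome SD units**

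- Unadjusted half-width = t(0.975, N − 2) × √(1/n1 + 1/n2)
- Adjusted half-width = t(0.975, N − 2 − q) × √(1/n1 + 1/n2) × √(1 − r²) × √((N − 3)/(N − 3 − q))

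The last factor is the expected cost of estimating the extra parameters.

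**45 and 23 analysed**

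- √(1/45 + 1/23) = 0.2563
- Unadjusted: 1.997 × 0.2563 = 0.512
- Adjusted, before the correlation term: 2.000 × 0.2563 × √(65/60) = 2.000 × 0.2563 × 1.041 = 0.533

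| r | √(1 − r²) | Adjusted half-width | Change from 0.512 |
|---|---|---|---|
| 0 | 1.000 | 0.533 | +4.2% |
| 0.3 | 0.954 | 0.509 | −0.6% |
| 0.5 | 0.866 | 0.462 | −9.7% |
| 0.7 | 0.714 | 0.381 | −25.6% |

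**Sensitivity**

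| Analysed | Unadjusted | r = 0 | r = 0.3 | r = 0.5 | r = 0.7 |
|---|---|---|---|---|---|
| 53 and 27 (none missing) | 0.471 | 0.487 | 0.465 | 0.422 | 0.348 |
| 37 and 19 (30% missing) | 0.566 | 0.596 | 0.569 | 0.516 | 0.426 |
| 40 and 40 (1:1, none missing) | 0.445 | 0.461 | 0.440 | 0.399 | 0.329 |

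The 1:1 row is there because the healthcare professional topic guide asks "How did you feel about 50% of the patients not receiving the JOINT SUPPORT intervention but getting normal care", which does not fit a 2:1 ratio. The relative gain is the same at either ratio.

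The number of sites matters little. The abstract mentions 12 healthcare professionals. At two per site that would be six sites and q = 7. For 45 and 23 the adjusted half-width before the correlation term is then 2.001 × 0.2563 × √(65/58) = 0.543. Multiplying by 0.954, 0.866 and 0.714 gives 0.518, 0.470 and 0.388 at r = 0.3, 0.5 and 0.7.

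**Summary rule.** If the contrast is unadjusted, a pooled SD can be recovered as half-width / (t × √(1/n1 + 1/n2)). If the contrast is adjusted, the same arithmetic yields a residual SD, not the SD of the outcome. Reporting the SD outright therefore matters more once adjustment is adopted.

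**The case against.** The strongest reply is that the article does not state what it is being criticised for. It neither calls the differences unadjusted nor excludes covariates, and an analysis plan that is not shown may specify them. This stands to the extent that unadjusted is a reading and not a quotation. It does not remove the point: the published sentence fixes a descriptive contrast, and a reader applying it as written would not adjust.

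The second reply is that little hangs on the estimate. The objective is secondary, no test is planned, and no row of Table 2 uses a treatment effect or its interval. An unadjusted difference is unbiased under randomisation, its interval already allows for chance imbalance, and stratification limits imbalance on site and age. All of this stands.

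The third reply is that the gain depends on a correlation the article does not give. That also stands: at r = 0.3 the gain is essentially nil, and at r = 0 adjustment costs a little.

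Three stronger readings are tempting, and the document does not support them.

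- A reader might infer that the effect estimate is biased or the trial invalid. It is neither; the issue is efficiency.
- A reader might infer that the SD and the baseline-outcome correlation would be estimated less precisely. Whether the contrast is adjusted does not change how well either is estimated from the same data.
- A reader might infer that the analysis must model the group classes with a random effect. Classes of three to five dyads exist in the JOINT SUPPORT arm only. With about 45 dyads in classes of about four there would be only some 11 classes (45 / 4), fewer if JOINT SUPPORT is the smaller arm. No intraclass correlation is given, so the class variance would be poorly estimated and the benefit is debatable.

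**Conclusion.** The point holds as a matter of precision and clear specification, not validity. The stated analysis is most naturally read as unadjusted, while baseline scores and two stratification factors are available at no extra data cost.

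With 45 and 23 analysed, adjustment for baseline, site and age group would shorten the 95% CI half-width from 0.512 SD to about 0.46 SD at r = 0.5 (about 10%) or 0.38 SD at r = 0.7 (about 26%), and hardly at all at r = 0.3. These figures rest on the assumed correlation, the 2:1 ratio, 15% missing, four inferred sites, and strata that add nothing beyond baseline.

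The either/or summary rule is a smaller, explicit defect: it omits the SD for skewed scales, although the SD can be roughly recovered from an unadjusted interval.

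The change is worth making because it is nearly free, but no progression decision depends on it.

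**What to change.** Replace the sentence on between-group differences with wording such as: for each continuous scale, the between-group difference with its 95% CI will be estimated by linear regression of the 3-month score on arm, adjusted for the baseline score, site and patient age group (<65/≥65); no formal testing will be undertaken. If the sponsor prefers unadjusted differences, the article should say so and give the reason.

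Change the summary rule so that mean and SD are reported for every continuous scale, with median and IQR in addition when the distribution is skewed. Report the baseline-outcome correlation for each scale, so that the definitive trial can be planned on it.

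**Cost.** A few sentences of text and no new measurements. The statistical price is a few degrees of freedom: if the covariates turn out not to be prognostic, the interval widens by about 3.5% with all 80 dyads analysed (0.471 to 0.487 SD), or about 4% at 45 and 23.

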#### Health economic

Data on healthcare use will be collected but not analysed. To answer the feasibility questions related to the health economic perspectives, we will test the completion of the health resource use questionnaire and will present the data descriptively.

#### Progression criteria

A ‘traffic light’ system (table 2) will be used as a guide for progression to a definitive trial.^35^ If any criteria are not met, they will be discussed by the trial oversight committee (TOC) to decide if a definitive trial is feasible with, or without, refinements.

### Qualitative study

The embedded qualitative investigation will assess intervention and study design acceptability for patients, caregivers and healthcare professionals.

#### Eligibility

The embedded qualitative study is optional for participants. Patients and caregivers will be able to express an interest to be approached regarding the qualitative substudy on the main study consent form at the beginning of the study. The sample will consist of patient–caregiver dyads and physiotherapists and occupational therapists who have delivered the JOINT SUPPORT intervention.

Dyads who have agreed to be contacted for an interview will be purposively sampled to ensure a maximum variation in: age, gender, presenting musculoskeletal pathology, ethnicity, duration of disability, severity of disability (as measured by the baseline MSK-HQ),^22^ relationship of caregiver to patient and duration the caregiver has been caring for the patient. Our intention is for caregivers and patients to be interviewed separately to enable them to more freely express their views but we will interview as a dyad if this is expressly requested.

We anticipate around 24 interviews will be conducted, involving approximately 12 patients/12 caregivers from the JOINT SUPPORT programme and approximately 8 caregivers/8 patients from the TAU group across the sites. Based on our previous research,^9^ this sample size should ensure a range of different viewpoints to reach information power^36^ to answer our feasibility questions.

The healthcare professionals delivering the JOINT SUPPORT intervention will be invited to participate in the voluntary interviews within 3 months of completing one participant through the JOINT SUPPORT programme. A minimum target of one physiotherapist and one occupational therapist who delivered the intervention will be invited to be interviewed from each site (eight participants in total). This will provide a range of contexts from different professional backgrounds. The healthcare professionals will be sent a PIS outlining the objectives and processes involved with this optional substudy. They will be asked to contact the research team by email if they are interested in participating. Those who express an interest will be contacted to arrange a mutually convenient time to conduct the interview.

#### Data collection

Interviews will aim to be conducted up to 6 weeks post-intervention via telephone or video call, at a time convenient to dyads and healthcare professionals. This allows exploration and reflection of the patients’ and caregivers’ study experience once the intervention has ended in a reasonable recall period. Interviews will be semi-structured, following an open-ended question schedule, with a maximum duration of 60 min. Open-ended questions will explore the acceptability of the research based on Sekhon *et al*’s^37^ acceptability framework including the values of the intervention, burden, perceived effectiveness, self-efficacy and suggestions for improvement from their perspectives. Interviews will be conducted by a qualitative researcher (AW), closely supervised by a senior qualitative researcher (SH).

Prior to conducting the interview, consent will be obtained and audio-recorded from the participant. The interview will then follow a semi-structured, open-ended question schedule (table 3; table 4). Broadly, participants will be asked their attitudes towards topics including the:

Timing, frequency, duration and content of the JOINT SUPPORT training programme and telephone booster calls.Support and training provided for the group-based programme and telephone boosters.Recording of both components of the JOINT SUPPORT programme.Logistic of managing the participant flow.Their views on the recruitment process.Acceptability of the JOINT SUPPORT programme.Potential modifications or recommended changes to the JOINT SUPPORT programme.Perceived effectiveness/helpfulness.

**Table 3 T3:** Interview topic guide for the caregiving dyad interviews

The interview will be structured on the following areas of interest	Sample questions
Introduction	Overall, could you share your experiences of being involved with our research?
Determining participant views of their intervention	First of all, can you talk me through what study treatment you received? (prompt—clarify what was JOINT SUPPORT and what was usual care/non-study intervention)
The approach and consent process and willingness to be randomised to either group	Can you talk me through how you got into the study? You were allocated to X group. What did that feel like? Could we have dealt with that differently?
The acceptability of the care (both groups)	Would you be happy to talk me through your treatment? As X’s carer, what was your impression of the care. For both of you, what was helpful and less helpful to your care?
Group-based JOINT SUPPORT programme and telephone booster calls (experimental group)	How far did you find the JOINT SUPPORT programme helpful—for both of you. Can you give specific examples? What didn’t work as well? Did you get the telephone calls from the trial team? Can you remember what you talked about? Can you give specific examples of what was helpful, and l helpful? Was there any advice that confused you or you weren't clear about?
What the strengths of the experimental intervention (perceived effectiveness)	What were the most helpful/good-bits of your JOINT SUPPORT intervention? What was good about it What didn’t you like about it?
What the weaknesses of the experimental intervention	What were the less helpful/worse bits of the JOINT SUPPORT intervention?
What modifications they may recommend to interventions received (standard care and experimental groups)	What could we improve? (prompt: What do you think is lacking?) How do you think we could better support you and your carer to support you with chronic pain?
The risk of intervention contamination between the groups	Did you talk to any other patients or caregivers while in hospital about the intervention? Was there any discussion between those who received it and did not receive it?
The ease and convenience of the data collection processes (baseline and 3 months) (all participants)	As you were part of a trial, we had to collect a lot of measurements. Can you talk me through what these were? How easy were they? How convenient were they? Overall, do you have any points to make about the testing?
Applicability of the methods and measures used	How did you manage with the questionnaires we gave you at the start of the study and at the end in the post? Were they easy to complete or do you remember them being a problem?

**Table 4 T4:** Interview topic guide for the healthcare professional interviews

The interview will be structured on the following areas of interest	Sample questions
Introduction (Perceived effectiveness)	Overall, could you share your experiences of being involved with our research?
The randomised to either group	How did you feel about 50% of the patients not receiving the JOINT SUPPORT intervention but getting normal care? Did this ‘sit easy’ with you?
The acceptability of the group-based care	How did the delivery of the JOINT SUPPORT group sessions go? How did you work out who would do what? Was there a decision on professional background? Did you feel comfortable teaching all the content? Were any modifications made? How did the patients and caregivers get on with it in your opinion?
JOINT SUPPORT telephone calls	How did you feel about doing the telephone calls? Were they helpful for caregivers and patients? Was it feasible to deliver one call to both members of the dyad? Did you make any modifications to the content of the call?
Training on intervention	Did you feel adequately prepared to deliver the group-based and telephone JOINT SUPPORT interventions? Would you recommend any changes to this? Did you need any additional ‘top up’ or ‘refresher’ training sessions?
The risk of intervention contamination between the groups	Do you think you used the JOINT SUPPORT intervention on control or non-trial patients? Did other professionals not in the trial use the intervention? If either occurred, do you think anything could have been done to avoid this?
The ease and convenience of the data collection processes	As you were part of a trial, we had to collect a lot of measurements. How easy were the intervention data collection logs? How convenient were they? What changes would you recommend if any were needed?

